#### **4.6.2.3. Cancer**

iNKT cell function is decreased in humans with cancer ([Tahir, 2001](#); [van der Vliet, 2008](#)), however, it is not clear whether the changes in iNKT cell function are a cause or result of the disease. In a study of subjects with multiple myeloma, the iNKT cell defect worsened with progression from pre-malignant to malignant disease, suggesting that iNKT cell defects are a result, rather than a cause, of cancer ([Fuji, 2003](#)). Mice deficient in iNKT cells do not exhibit increased incidence of spontaneous cancer, but they do show increased susceptibility to numerous experimental cancers ([Berzofsky, 2009](#)). Increased incidence of cancer in two strains of mice with a genetic absence of iNKT cells has also been observed ([Swann, 2009](#)). Conversely, in murine models of cancer, there is a clear therapeutic benefit of iNKT cell activation by  $\alpha$ GalCer ([Chang, 2007](#)) or adoptive transfer of iNKT cells. There is limited evidence to suggest that iNKT cell deficiency increases the risk of cancer in mice, absent a strong genetic predisposition ([Renukaradhya, 2008](#)). Finally, there are no data regarding the role of transient iNKT cell depletion and the risk of cancer.

#### **4.6.2.4. Enhanced autoimmunity**

The role of iNKT cells in regulating autoimmunity is controversial, as evidence supporting both a protective and adverse role for these cells in preclinical models of autoimmune disease can be found ([Wu, 2009](#)). J $\alpha$ 18 knockout mice (that lack iNKT cells and some of the T cell repertoire) do not develop overt autoimmune disease, but they do develop anti-DNA antibodies ([Sireci, 2007](#)). In many human autoimmune diseases, peripheral iNKT cell numbers are decreased, and in some cases functional defects have been identified ([van der Vliet, 2001](#)). As is the case with cancer, what is not well-understood is whether these abnormalities are a cause of the disease or a consequence of the disease or its treatment.

#### **4.6.2.5. Fertility and embryogenesis**

The role of iNKT cells in embryogenesis, reproduction, and spermatogenesis is not well understood. Mice that lack iNKT cells have normal fertility and pregnancies.

Reproductive toxicology studies have not yet been performed with NKTT120. Subjects of child-bearing potential are required to use appropriate birth control methods. Pregnant and breast-feeding women should not receive NKTT120. Women of child-bearing potential desiring to become pregnant should not receive NKTT120 or should wait for the elimination of NKTT120 from the circulation and the recovery of peripheral iNKT cells before becoming pregnant. The effect of NKTT120 on normal spermatogenesis is unknown.

#### **4.6.3. Potential risk specific to adults with SCD and risk mitigation**

The potential risks associated with administration of NKTT120 may be enhanced by the pathophysiology of SCD. Subjects with clinical or subclinical organ damage due to SCD may

have a worse outcome following an AE than healthy subjects without SCD. Subjects will undergo routine pre-screening for evidence of end organ damage and subjects with clinical evidence of significant end organ damage will be excluded from participation in the trial.

Patients with SCD are functionally asplenic and are at risk for infection with encapsulated bacterial organisms. Subjects with ongoing infections will be excluded from the study. All subjects must have received CDC-recommended immunizations for adults, including immunizations for streptococcus pneumonia (Pneumovax) and *N. meningitides* [Meningococcal conjugate vaccine, quadrivalent (MCV4)] unless contra-indicated (see Section 18.1). While prophylactic antibiotics are generally not used in adults with SCD, subjects currently taking prophylactic antibiotics will be allowed to participate without discontinuing prophylactic antibiotics. Subjects not currently taking prophylactic antibiotics will not be required to start prophylactic antibiotics. Subjects will be monitored throughout the study for infections.

Due to the potential risk of activation of latent TB infections, subjects will be screened for recent exposure to TB and for evidence of active or latent TB by QuantiFERON-Gold® test and chest X-ray (CXR). Subjects with a history of infection with atypical mycobacterium will be excluded from the study.

Due to the potential risk of viral infection exacerbations during the period when iNKT cells are depleted, subjects will be screened for recent exposure to childhood viral diseases, including varicella, or exposure to influenza prior to enrollment and must be current on all CDC-recommended viral immunizations for adults. The CDC recommendations for adult immunizations are provided in section 18.1. Subjects will be monitored clinically for viral infections (especially Herpesvirus family viruses) throughout the study.

Subjects with a history of cancer will be excluded from the study and subjects in the study will be clinically monitored for the emergence of cancers during follow-up, until one month after recovery of iNKT cells.

Subjects with a known autoimmune disease (including type 1 diabetes) will be excluded from the study. All subjects will be monitored for treatment-emergent signs of autoimmune disease. Serum for evaluation of autoantibodies will be stored for future analysis of autoantibody status. These samples will be used to confirm a diagnosis of a new autoimmune disease or drug-induced lupus.

#### **4.7. Subject population and study rationale**

The planned Phase 1 study will be performed in adults with “stable” SCD, defined as not having experienced acute pVOC, ACS or other major or significant SCD-associated event requiring hospitalization or outpatient medical care during the month prior to enrollment. The stable SCD population was specifically chosen as appropriate for the first-in-human study because the primary goal of the Phase 1 study is to evaluate the safety profile of NKTT120 and to determine the MTD or the recommended dose for future clinical trials, in a relevant population. Healthy volunteers who are frequently enrolled in Phase 1 studies, were not selected for evaluation of NKTT120 because they do not show increased numbers of iNKT cells or activated iNKT cells in the peripheral circulation. Therefore, determination of the MTD and safety profile in healthy volunteers might not be relevant to the SCD population. NKTT120, by specifically depleting only iNKT cells, has the potential to decrease the inflammatory component associated with IRI and to

decrease acute pVOC and ACS events. In the longer-term, chronic pain, AHR, and end organ damage may be improved, thus leading to an improved QoL for SCD patients.

#### **4.8. Dose Rationale**

In selecting a starting dose and planned range of doses to be studied, consideration was given to the maximum recommended safe dose (MRSD) calculated using standard approaches (FDA Guidance for Estimating the Maximum Safe Starting Dose in Initial Clinical Trials for Therapeutics in Adult Healthy Volunteers), evaluation of safety factors, and an anticipated pharmacologically active dose (PAD).

The human equivalent dose (HED) to the No Observed Adverse Effect Level (NOAEL) determined in the GLP repeat dose toxicology study in cynomolgus monkeys was 3.2 mg/kg. Using a 10-fold safety factor, the MRSD is 0.32 mg/kg. The HED of an expected PAD is 0.001 mg/kg. Therefore, the planned starting dose of 0.001 mg/kg is 1/300th of the MRSD and 1/3,000th of the NOAEL.

The highest planned study dose of 0.1 mg/kg is 1/3rd of the MRSD. Therefore, the planned dose range provides for an expected margin of safety at the lowest and highest doses. However, as described in [Sections 6.1](#) and [6.6](#) of this protocol, the planned doses may be revised based on the evolving understanding of both safety and pharmacologic activity obtained throughout the study.

#### **4.9. Choice of Dose Escalation Interval**

This study incorporates a two-week interval to ensure subject safety in an existing cohort before escalating the dose in a new cohort. This time interval was chosen as a result of:

- Preclinical in vitro studies, and in vivo studies in non-human primates that show the lack of cytokine release phenomenon or adverse impact of iNKT cell depletion over a wide range of doses, repeat dosing and follow-up periods, and
- The time period when iNKT cell-related DLT events might occur, as a direct result of either the NKTT120 antibody infusion, or the consequently rapid reduction in iNKT numbers (<24 hours) and its consequent effect on SCD. Safety issues related to prolonged iNKT depletion as a result of high doses of NKTT120 are also a consideration, and are discussed in detail below. The safety monitoring plan provides for subject safety in this phase 1 SAD trial in that the SRC will be immediately aware of all SAEs and reviewing all AEs on a routine basis as subjects are followed through 30 days after iNKT cell recovery.

A wide dose range of NKTT120 has been administered to cynomolgus monkeys as the most relevant responsive species, and no obvious acute or chronic adverse clinical responses to NKTT120 treatment have been observed. Importantly, there have been no acute or chronic elevations of cytokines that would be associated with systemic iNKT cell activation with observations of 1 day to >20 weeks post dosing, conservatively supporting the safety of a 2 week dosing interval between cohorts.

To provide highest levels of subject safety, the SRC will be intensely evaluating subjects on an ongoing basis post dosing for the two types of potential toxicities:

- 
- NKT-specific dose limiting toxicities such as cytopenias, infections, and cytokine storm syndrome
  - Sickle cell-specific dose limiting toxicities such as hemolysis, acute vaso-occlusive episodes, any provider encounter (clinic, ED or hospital) for increased pain in the extremities, chest, abdomen or head lasting for at least 2 hours, requiring opioid administration that cannot be explained except by sickle cell disease.

This trial initiates dosing at 0.001 mg/kg, a dose 1/300th the maximum recommended starting dose (MRSD) based on the 10 mg/kg no observed adverse effect level (NOAEL) determined from the repeat dose GLP toxicology study, and 1/3000th the human equivalent NOAEL dose. The highest dose we propose to administer in this study, 0.1 mg/kg, is 1/3 of the MRSD (0.32 mg/kg) estimated from the NOAEL determined in the repeat dose toxicology study. The lack of significant toxicity within the 1-3 months of high exposure of NKTT120 achieved in this study supports our proposed dosing interval.

The primate data derived from the 28 day toxicology study and the single dose depletion recovery study show that NKTT120 ADCC-mediated iNKT cell depletion is maximal within one day, and suggest that the duration of the effect is related to the plasma concentration necessary to eradicate regenerating iNKT cells as well as to the extent of iNKT cell pool depletion. At the lower levels, the doses proposed for this trial should only provide peripheral depletion of iNKT cells, and are not expected to result in complete tissue depletion. The safety profile in monkeys, together with the fact that the iNKT cell is the only target for NKTT120 argue that despite the estimated human half-life of NKTT120 of ~22 days (based on the 11 days half-life observed in monkeys), one would not expect to see additional adverse effects from the decreasing levels of the antibody alone. The data from the single dose depletion recovery study suggests that iNKT cells recovery will occur in all subjects.

Through their effects on other immune cell subsets (dendritic cells, NK, T cells and B cells), iNKT cells have been implicated in a wide variety of physiological and pathophysiological processes {[Matsuda, 2003](#); [Nakai, 2004](#); [Fujii, 2003](#); [Fujii, 2007](#); [Yoshimoto, 2003](#); [Galli, 2003](#); [Chang, 2012](#); [King, 2012](#); [Wu, 2009](#); [Berzofsky, 2009](#); [Tupin, 2007](#)). Thus, chronic suppression of iNKT cells poses potential risks, as iNKT cells are thought to play a role in the response to pathogens, in immune surveillance for cancer, and in the regulation of autoimmunity ([Wu, 2011](#); [Balato, 2009](#)). However, studies in mice and humans evaluating the role of iNKT cells in infection, cancer and autoimmunity have yielded conflicting results. Tools such as various knockout mice that lack iNKT cells, and the synthetic glycolipid,  $\alpha$ -GalCer, have helped to define the role of iNKT cells in health and disease; however, disease model studies in mice have been hampered by the lack of a mAb that specifically recognizes the murine iTCR. In addition, there are significant differences between mice and humans with respect to the CD1 repertoire, the lipid antigen-presenting MHC class I-like molecules, and iNKT cell distribution and function ([Bendelac, 1997](#)), which have made extrapolation from mouse to human extremely difficult. While infection is a theoretical risk of prolonged iNKT cell depletion, and probably of the greatest concern in this patient population, there is little evidence to suggest that a lack of iNKT cells increases the risk of predisposition to infection in preclinical models ([Berzins, 2011](#)).

Even if prolonged iNKT cell depletion were to result in an increase in the risk of infection, it would likely need to be a markedly increased risk in order for it to be detected in a small, single

---

dose study in an at-risk population. If there is a dramatic increase in susceptibility to infection, it will likely emerge in the first two weeks of iNKT cell depletion, and further increasing the dosing interval between cohorts will neither have a material impact on our ability to detect such a DLT, nor meaningfully reduce the clinical risk to subjects in the proposed study.

#### **4.10. Study conduct**

The following characteristics of an adequate and well-conducted trial will be implemented:

1. The investigators will be well-qualified by scientific training and experience
2. Detailed electronic Case Report Forms (eCRFs) will be completed for every subject
3. Requirements for institutional review as set forth in ICH E6 and Good Clinical Practice (GCP) guidelines, and Title 21 Code of Federal Regulations (CFR), Part 56 will be followed
4. Requirements for informed consent set forth in ICH E6 (GCP) and 21 CFR, Part 50 will be followed
5. Safety data will be recorded and evaluated
6. Routine monitoring visits will be conducted by the Sponsor's representative to ensure data accuracy

This trial will be conducted according to the US Food and Drug Administration 21 CFR, Part 50, ICH Harmonized Tripartite Guidelines for Good Clinical Practice (Guidance E6), the [Declaration of Helsinki \(18.3\)](#) and all local laws and regulations concerning clinical studies and the protection of study subjects under the sponsorship of NKT Therapeutics Inc.

## **5. TRIAL OBJECTIVES AND PURPOSE**

### **5.1. Primary objective**

The primary objective is to assess the safety and MTD, or RDL for Phase 2, of a single ascending dose of IV NKTT120 in adult subjects with stable SCD. If the highest dose level is reached without determining a MTD, the RDL(s) for phase 2 will be determined by a dose that is at or below the highest dose and which is associated with iNKT cell recovery that allows dosing every 4-6 months in phase 2 studies.

### **5.2. Secondary objectives**

1. To assess the PK profile of IV NKTT120
2. To assess the PD profile of peripheral iNKT cell depletion and recovery following IV NKTT120, including the recovery of the population of activated iNKT cells as measured by the expression of CD 69.
3. To evaluate change in clinical measures of SCD activity (e.g., leukocyte counts, Hgb, reticulocytes, platelets, LDH, hsCRP)
4. To evaluate the effect of NKTT120 on daily pain and use of analgesic medication compared to screening values (e.g., 2-week screening run-in daily pain score and analgesic use)
5. To evaluate the effect of the administration of NKTT120 on AHR comparing PFTs (including FVC, FEV1, FEF25-75%) and PEF to screening values
6. To evaluate changes in QoL and pain compared to screening values (ASCQ-Me, PROMIS short-form and eSCaPe e-Diary).
7. To explore a number of serum and cellular biomarkers of inflammation, coagulation and endothelial function (e.g. IFN $\gamma$ , TNF $\alpha$ , IL1 $\beta$ , IL-6, IL-8, sPLA2, sP-selectin, F1+2, D-dimers and vWF) compared to screening values
8. To evaluate anti-drug antibodies (ADAs) following single dosing

#### **5.2.1. Pharmacokinetic (PK) and pharmacodynamics (PD) objectives**

The PK objective is to determine the PK profile of NKTT120 and the relationship of PK to depletion and recovery of iNKT cells, adverse event profile and presence of ADAs.

The PD objective is to determine the profile of iNKT cell depletion and recovery post-dosing with NKTT120 and to correlate the PK and PD profiles. It is anticipated that iNKT cells will recover after NKTT120 is eliminated from or at present at very low concentrations in the serum.

### **5.3. Biologic activity and biomarker objectives**

To investigate the biologic activity of NKTT120, a number of clinical assessments will be performed. These assessments will be evaluated pre- and post-dosing at appropriate intervals and will be correlated with the PK/PD profile of NKTT120. They include:

- 
1. Clinical measures of SCD activity (e.g., leukocyte counts, hemoglobin, reticulocytes, platelets, LDH, CRP)
  2. Pain frequency and intensity and use of analgesics as recorded daily in an eDiary
  3. AHR and use of SABA, both recorded daily in an eDiary, and additional assessment of AHR determined by PFTs at clinic visits
  4. QoL as determined by PROMIS short form and ASCQ-Me questionnaires administered in the clinic

To explore the biologic effects of depletion of iNKT cells on biomarkers of inflammation, coagulation, endothelial activation, and a number of serum and cellular biomarkers will be assessed (e.g., IFN $\gamma$ , TNF $\alpha$ , IL-1 $\beta$ , IL-6, IL-8, F1+2, D-dimers, vWF, sPLA2 and sP-selectin) pre- and post-dosing at clinic visits. Results will be correlated with the PK/PD profile of NKTT120.

#### **5.3.1. Immunogenicity objective**

To determine the immunogenicity of NKTT120, the presence or absence of ADAs will be determined in blood samples taken pre-dosing and at the EOS visit.

## **6. INVESTIGATIONAL PLAN**

### **6.1. Overall Study Design**

This is an open-label, multi-center, SAD Phase 1 study aimed at determining the MTD or RDL for Phase 2 of intravenously administered NKTT120 in adult subjects with stable SCD. For the purpose of this protocol, stable SCD is defined as not having experienced acute pVOC or ACS or other SCD-associated event requiring hospitalization or outpatient care within one month prior to dosing. In addition to determining the safety profile of NKTT120 in subjects with stable SCD, this study will also examine pain, analgesic use, QoL, pulmonary function, and inhaled SABA use. During the two-week screening run-in period and throughout the follow-up, subjects will keep a daily eDiary for pain, analgesic use, and inhaled SABA use. The ASCQ-Me and PROMIS QoL questionnaires will be administered at clinic visits. The screening run-in outcomes will be used as baseline comparison for values obtained post-dosing.

The study will evaluate single doses that are escalated over a range from 0.001 mg/kg to 0.1 mg/kg (0.001, 0.003, 0.01, 0.03, and 0.10 mg/kg). As the study progresses, the current dose escalation plan of approximately half log increment may be reduced to a slower arithmetic increment of dose escalation without increasing the number of maximum subjects if information about iNKT cell recovery times from the lower dose cohorts suggests it is necessary. Similarly, a dose de-escalation using 3+3 enrollment will be applied if indicated by the data and recommended by the Clinical Investigators and/or SRC.

Only one subject will be dosed per day and each subject will remain in the clinic for at least 6 hours after dosing for evaluation of any acute toxicity (i.e., infusion reactions, CRS, or allergic reactions) and for collection of post-dosing blood samples. Should CRS of any type be observed in subjects in any cohort, premedication with acetaminophen (1000 mg), histamine 2 (H2) receptor antagonists (diphenhydramine, 50 mg) and corticosteroids may be initiated prior to dosing of subsequent subjects to lessen the severity of CRS.

Dose escalation will be governed by a 3+3 design as follows:

- Dosing will begin at the lowest dose (minimally effective dose level), with 3 subjects per cohort.
- Each subject in the cohort must have completed at least two weeks of follow-up post-dosing before the first subject in the next cohort is dosed.
- If 0 of 3 subjects in the cohort experiences a DLT, escalation to the next dose level cohort may proceed.
- If 1 of 3 subjects in the cohort experiences a DLT, 3 additional subjects will be added to the cohort.
- If  $\geq 2$  of 3 - 6 subjects experience a DLT, the MTD has been exceeded and dose escalation will cease. Three (3) subjects will be added to the previous lower dose cohort(s). The MTD is defined as the highest dose at which no more than one of six subjects experiences a DLT in the dose cohort.

A SRC will review all safety and laboratory data on all subjects in the study at regular intervals. The SRC will also be made aware of any adverse EOs that could be potential DLTs and any SAEs as soon as they are reported. Because of the complex nature of the disease, before any EO is determined to meet DLT criterion, the SRC will meet, ad hoc, to review the safety data for an individual before declaring the event is a DLT or not. While the SRC is determining if a DLT has occurred, no additional subjects will be enrolled.

The SRC will also assess safety signals that may become evident in the longer-term follow-up and will make recommendations to the Sponsor regarding study conduct and risk mitigation, as well as dose de-escalation protocol changes.

Note that peripheral iNKT cells will be followed as a pharmacodynamic marker of drug activity and that depletion of iNKT cells is an expected outcome and will not be considered a DLT. Acute pVOC and ACS or other SCD-associated AEs (e.g., hemolysis, hepatic/splenic sequestration, decreased haptoglobin, hemoglobinuria, bone pain, chest wall pain, pain in the extremity, priapism in men, gall stones, leg/ankle ulcers, avascular necrosis of bone, stroke, cognitive disabilities) will not automatically be considered DLT, but will be evaluated on a case-by-case basis and may be elevated to DLT status if warranted and related to NKTT120. This decision will be made by the SRC.

The primary endpoint (MTD or RDL) will be completed when the last subject dosed completes dosing plus two weeks of follow-up (time at which next cohort would have started). However, each subject will be followed until 1 month after their iNKT cells have returned to detectable levels. If the highest dose level is reached without determining a MTD, the RDL(s) for phase 2 will be determined by a dose that is at or below the highest dose and which is associated with iNKT cell recovery that allows dosing every 4-6 months in phase 2 studies.

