### **6.2.2. Treatment and follow-up**

Treatment consists of a single IV dose of NKTT120 administered slowly over ten (10) minutes. Each subject will be followed until one month after iNKT cells have recovered to detectable levels. Total duration of follow-up post-dosing will vary based on the dose level received. Currently it is anticipated that iNKT cells will return to detectable levels within 1 month after NKTT120 is no longer detectable in the serum; in the lower dose cohorts; at the highest dose (0.1 mg/kg) this could be  $\geq 6$  months based on preliminary PK in non-human primate).

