### **6.3.2. Secondary Endpoints**

#### **6.3.2.1. Pharmacokinetic (PK) Profile and Pharmacodynamic (PD) Endpoints**

Calculated PK parameters for NKTT120 will be determined, including  $C_{\max}$ ,  $C_{\text{avg}}$ , AUC,  $t_{1/2}$ , and  $V_d$ .

The PD endpoint consists of iNKT cell depletion and recovery after dosing with NKTT120. Recovery is defined as the detectable presence of iNKT cells.

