**Study Design Notes**

- 2-30 subjects
- NKTT will make dose escalation decisions with input from Scientific Review Committee
- MTD or RDL will not be complete until the last subject dosed in a cohort completes dosing plus two weeks of follow-up
- All subjects will be followed until 1 month AFTER their iNKT cells have returned to detectable levels
- If highest dose level is reached without determining a MTD, then the RDL for Phase 2 will be the dose that is at or below the highest dose and which iNKT cell recovery will allow dosing every month or every other month in Phase 2 study

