### Escalation scheme

Five dose levels of NKTT120 will be assessed. Each dose level will be administered as a single ascending IV dose. The dose levels to be investigated are 0.001, 0.003, 0.01, 0.03 and 0.1 mg/kg.

A standard dose escalation Fibonacci 3+3 design will be employed. Initially, three subjects will be treated. If no subject experiences DLT, dosing will escalate. If one subject experiences DLT, 3 additional subjects will be treated at the current dose and escalation will occur only if no more than 1 of 6 subjects experiences DLT. If  $\geq 2$  of 3 - 6 subjects experiences DLT at the initial dose level of 0.001 mg/kg, then it may be de-escalated. The study continues until MTD has been determined, or the highest dose cohort is filled. If no MTD is reached, RDL will be determined based on the overall safety profile of NKTT120 and the duration of iNKT cell depletion. The RDL(s) for phase 2 will be determined by a dose that is at or below the highest dose tested which is associated with timing of iNKT cell recovery that allows dosing every 4-6 months in phase 2 studies. The dose-level cohort that represents the RDL will be expanded to 6 subjects to confirm the RDL. [Table 5](#) below provides the probability of dose escalation.

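### Section 6.1 gives the MTD and the RDL one completion time, two weeks after the last dose; this suits the MTD but not an RDL defined by iNKT recovery over 4-6 months

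*Protocol*

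**What the plan says.** Section 6.1 sets one time for both forms of the primary endpoint: "The primary endpoint (MTD or RDL) will be completed when the last subject dosed completes dosing plus two weeks of follow-up". It explains this as the moment the next cohort would have opened. The next sentence treats longer follow-up as something apart: "However, each subject will be followed until 1 month after their iNKT cells have returned to detectable levels".

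The notes under Figure 1 use the same two weeks, worded as a minimum: "MTD or RDL will not be complete until the last subject dosed in a cohort completes dosing plus two weeks of follow-up".

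When no MTD is found, the RDL depends on recovery. Section 5.1 requires "iNKT cell recovery that allows dosing every 4-6 months in phase 2 studies", and Sections 6.1, 6.3.1 and 12 repeat this. Section 12 adds that "RDL will be determined based on the overall safety profile of NKTT120 and the duration of iNKT cell depletion". Section 6.3.2.1 says "Recovery is defined as the detectable presence of iNKT cells". Of the time to recovery, Section 6.2.2 says "at the highest dose (0.1 mg/kg) this could be" six months or more.

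Sections 6.2 and 12 also say "The dose-level cohort that represents the RDL will be expanded to 6 subjects to confirm the RDL". Neither says when that cohort is identified.

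**The concern.** The two-week period is justified in Sections 4.9 and 6.6.1 as the time in which acute dose-limiting events should appear. An MTD read from DLT counts can be complete then. An RDL read from the duration of depletion cannot, unless recovery has already been seen at the doses being compared. Section 6.1 nevertheless puts both under one clock, and nothing elsewhere overrides it for the RDL.

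This matters because the RDL is the likely primary result. Section 4.8 puts the top dose at one third of the maximum recommended dose derived from the monkey NOAEL, and Section 4.4 reports no adverse events in the monkey studies. If the choice between 0.03 and 0.1 mg/kg were made at the stated point, it could rest on predicted rather than observed recovery at 0.1 mg/kg. The three confirmation subjects could then be added to a cohort that later proves not to be the RDL.

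**Working it through.** The two-week point has no formula behind it, so there is no figure to reproduce. The check compares follow-up available at that point with what the RDL criterion needs.

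**Inputs.** Five cohorts of three (Section 12). One subject per day and 14 days between cohorts (Section 6.1). Dosing on Mondays or Tuesdays only (Section 6.2.1). Study dates 2/1/2013 to 8/1/2014, which is 546 days (synopsis). Criterion of 4-6 months, taken as 120-180 days with 30-day months.

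**Fastest pace.** Subjects are dosed on cohort days 0, 1 and 7, so each cohort takes 7 + 14 = 21 days. The 0.1 mg/kg cohort starts on Day 4 × 21 = 84 and is dosed on Days 84, 85 and 91. The stated completion is 91 + 14 = Day 105.

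**Even spread over the planned study (assumed).** Allow 180 days to recovery plus 30 to the final visit after the last dose: (546 − 180 − 30 + 14)/5 = 70 days per cohort. Assume dosing on cohort days 0, 28 and 56. The 0.1 mg/kg subjects are dosed on Days 280, 308 and 336, and completion is 336 + 14 = Day 350.

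| Pace | Completion | Follow-up at 0.1 mg/kg (days) | Follow-up at 0.03 mg/kg (days) |
|---|---|---|---|
| Fastest | Day 105 | 21, 20, 14 | 42, 41, 35 |
| Even spread | Day 350 | 70, 42, 14 | 140, 112, 84 |

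With six per cohort at the fastest rate, completion is Day 155 and the 0.1 mg/kg subjects have 14-29 days.

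**Expected recovery at 0.1 mg/kg.** In monkeys, cells were first measurable at week 10, or 70 days (Section 4.4). Doubling for the half-life ratio of 22 to 11 days (Section 4.9) gives 140 days; that scaling is an assumption. Section 6.2.2 itself allows six months or more.

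**Shortfall for the last subject.** 120 − 14 = 106 days to 180 − 14 = 166 days.

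**Effect of the expansion to six.** If the last subject dosed is an expansion subject, the completion point moves:

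- Expansion at 0.1 mg/kg straight away, fastest pace: last dose on Day 105 + 7 = 112, completion Day 126, and the first three 0.1 mg/kg subjects have 42, 41 and 35 days.
- Expansion straight away, even spread: last dose on Day 350 + 56 = 406, completion Day 420, and the first three have 140, 112 and 84 days. The cohort to expand was still chosen at Day 350.
- Expansion after 180 days of follow-up, three subjects over 7 days (weekday rounding ignored): last dose on Day 91 + 187 = 278 or 336 + 187 = 523, completion Day 292 or 537. The first three then have 201-208 or 201-257 days, which is enough.

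**If the wrong cohort were expanded.** With no DLTs, the one-sided 95% upper bound on the DLT rate at the true RDL is 1 − 0.05^(1/3) = 63% for 0/3, against 1 − 0.05^(1/6) = 39% for 0/6. These bounds matter only if the RDL is picked without waiting for recovery.

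**The case against.** The strongest reply is that Section 6.1 can be followed literally without harm. Observe recovery, choose the RDL, expand to six, then wait two weeks after the last expansion subject. On that order the first three 0.1 mg/kg subjects have more than 200 days of follow-up at the stated point. The Figure 1 notes word two weeks as a minimum, the RDL definition itself demands recovery data, and every subject is followed until one month after recovery.

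Much of this stands. A reader might infer that no 0.1 mg/kg subject can have shown recovery when the endpoint is declared complete. The documents do not support that. Accrual time is not capped, expansion may be delayed, and the shortfall is certain only for the last subject dosed. Nor does any section instruct the sponsor to pick the RDL at two weeks, and the two-week DLT interval is not at fault.

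The reply does not remove the conflict. The benign order is nowhere stated. Section 6.1 ties its time to the opening of the next cohort, which is the DLT clock, and sets follow-up to recovery apart from the endpoint. The cohort must be chosen before it is expanded, and no section says the choice waits for recovery.

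**Conclusion.** The point holds as a conflict between a stated completion time and the endpoint's own definition. Two weeks after the last dose fits the MTD and does not fit the RDL. If the RDL is declared two weeks after the third 0.1 mg/kg subject, with no wait before expansion, that subject is 106-166 days short of the criterion. At the fastest pace with three per cohort, all three have only 14-21 days, less even than the 70 days at which monkey cells first reappeared.

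The 120-180 days assumes the 4-6-month interval. Cells returning earlier would be seen earlier, so this is the span over which the criterion is judged, not a fixed wait. The Figure 1 notes give a different interval, every month or every other month, but that too exceeds 14-21 days. The even-spread schedule is an assumption.

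The consequence is a possible premature choice or misdirected expansion. Escalation, DLT assessment and data collection are unaffected.

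**What to change.** - In Section 6.1 and the Figure 1 notes, limit the two-week point to completion of the DLT/MTD component.
- State that the RDL is selected only once recovery, or 6 months of follow-up, has been observed in the candidate RDL cohort and the highest-dose cohort. How many subjects in each must reach that point can be left to the sponsor and the Safety Review Committee.
- In Sections 6.2 and 12, state that expansion to six follows that selection, or is provisional and repeated at the final RDL if it differs.
- Align the dosing interval in the Figure 1 notes with the 4-6-month criterion.

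No new assessments are needed, since iNKT sampling already runs monthly until recovery. The cost is time: the RDL is declared about 106-166 days later than Section 6.1 literally says. If expansion waits for 180 days of follow-up and expansion subjects also take 180 days to recover, the last final visit falls on Day 278 + 180 + 30 = 488 at the fastest pace, within the planned 546. At the even-spread pace it falls on Day 523 + 210 = 733, which is 187 days over. Provisional expansion avoids that delay unless the first choice proves wrong, and without DLTs uses at most 5 × 3 + 3 + 3 = 21 of the 30 subjects.
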